**Methods:**

A randomized, placebo-controlled clinical trial was designed to assess the impact of the Synergy 1 on paediatric CD patients following a GFD. We randomized 34 children diagnosed with CD into an intervention group receiving 10 g of the Synergy 1 supplement daily and a placebo group (receiving maltodextrin) during a 12-week nutritional intervention. Selected biochemical parameters, nutritional status and the characteristics of faecal bacteria will be determined in samples collected before and after the intervention. Analysis of vitamins and amino acids concentration in biological fluids will allow to assess the dietary intake of crucial nutrients. The compliance to a GFD will be confirmed by a Food Frequency Questionnaire (FFQ-6) and the analysis of serum anti-tissue transglutaminase and faecal gluten immunogenic peptides (GIP).

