
### Data collection

Data were collected during the enrolment visit (T0), a visit at the end of the intervention (T1) and regular follow-up visits that took place every 3 months in the Gastroenterology Clinic. Demographic data were collected during the T0 visit. Anthropometric data and biological samples (blood, urine and faeces) were collected during T0 and T1 visits. The participants were provided with sterile containers for collecting urine and stool samples. An assessment of GFD compliance during the trial was performed at the end of the study.

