### Analysis of morphological and biochemical blood parameters

The complete blood count, blood biochemical parameters (creatinine, aspartate aminotransferase - AST, alanine aminotransferase - ALT, C-reactive protein – CRP, albumin, protein, calcium, phosphorus, magnesium, sodium, potassium, chloride, ferritin), tTG and urine biochemistry parameters (creatinine, calcium, phosphorus, magnesium, sodium, potassium) were analysed according to standard procedures in the Hospital’s Department of Laboratory Diagnostics and Transfusion Serology. The content of fat-soluble vitamins in plasma will be determined by a chromatographic method (HPLC-DAD for vitamins A and E) or in the enzyme-linked immunosorbent assay (ELISA) for vitamin D, using commercial kits. The content of water-soluble vitamins (B1, B2, B6, B9, B12) in plasma will be assayed using the HPLC-DAD method. The profile of amino acids in plasma will be analysed via EZ:Faast™ derivatisation method followed by gas chromatography/mass spectrometry detection (GC-MS). All parameters will be analysed at the beginning and at the end of the study.

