### Gut microbiota characteristics, short-chain fatty acids and GIP concentration

Bacterial genomic DNA will be isolated from faecal samples with the use of a dedicated commercial kit (GeneMATRIX Stool DNA Purification Kit, EURx, Gdańsk, Poland) for a quantitative analysis of gut microbiota. The quantitative characteristics of intestinal bacteria will be determined using the Real-Time PCR technique and group-specific primers. The DNA of strains representing the predominant bacterial groups will be the positive control, and it will be used to develop the standard curve. The total counts of *Bifidobacterium, Bacteroides*-*Prevotella*-*Porphyromonas, Clostridium coccoides, C. leptum* and *Lactobacillus* communities will be determined.

The concentration and profile of short-chain fatty acids (SCFAs), which are indicative of the activity of gut microbiota, will be determined in the faecal samples of all participants by gas chromatography with a flame ionization detector (GS-FID).

A quantity of GIP in faecal samples will be determined using a commercial Sandwich ELISA kit (Biomedal Diagnostics, Sevilla, Spain). Gut microbiota profiles, SCFAs and GIP concentration analysis will be performed in the faecal samples collected at T0 and T1 visits.

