### Statistical analysis

Anthropometric and demographic data will be analysed using descriptive statistical methods. The participants whose reported intake of the Synergy 1 supplement or the placebo exceeded 80% of the prescribed intake will be included in final analyses. Statistical analyses will be performed in duplicate and expressed as mean values and standard deviation (SD). The influence of prebiotic supplemented-GFD and placebo supplemented –GFD on the measured parameters will be determined by one-way analysis of variance (ANOVA). If the differences between experimental and placebo groups are statistically significant (*P* < 0.05), the data will be subjected to post-hoc comparisons with the use of Fisher’s Least Significant Difference (LSD) test. The side effects of supplementation will be expressed by the percentage of each effect noted in the experimental group or the placebo group. The average consumption of food products by CD children during the intervention trial obtained from FFQ-6 will be compared in the Kruskal-Wallis test. Data will be processed statistically using Statistica 12 software (StatSoft, USA).

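### The supplement's effect is tested by one-way ANOVA with Fisher's LSD and no T0 term, although blood, urine and faecal outcomes are measured at T0 and T1; ANCOVA on T0 would be more efficient at no data cost.

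*Protocol article*

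**What the plan says.** The Statistical analysis section names one test for the supplement's effect. The influence of the prebiotic-supplemented and placebo-supplemented diets "on the measured parameters will be determined by one-way analysis of variance (ANOVA"). The next step is conditional: "If the differences between experimental and placebo groups are statistically significant (*P* < 0.05"), then "the data will be subjected to post-hoc comparisons with the use of" Fisher's "Least Significant Difference (LSD) test". No T0 covariate, change score, paired test or repeated-measures term appears. The section does not say whether the response is the T1 value, the change from T0, or both visits together. The same section handles anthropometric and demographic data descriptively, so they fall outside this point.

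The data are before-and-after data. The abstract says that the biochemical, nutritional and faecal measures "will be determined in samples collected before and after the intervention". Data collection says that biological samples "were collected during T0 and T1 visits". The blood section adds: "All parameters will be analysed at the beginning and at the end of the study". The Urine analysis section covers both visits, and microbiota, short-chain fatty acid and GIP analyses "will be performed in the faecal samples collected at T0 and T1 visits".

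Under Randomization and blinding there are two arms, 18 and 16 children, with randomisation stratified by gender and age. The Sample size section calls the trial a pilot without a sample size calculation, expects 12 completers per arm, and will use the results to size a fully powered study.

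**The concern.** A one-factor model without T0 leaves unused the most informative covariate that the trial collects. The children are 4 to 17 years old at baseline, and the Discussion lists the wide age span and differing duration of gluten-free diet as limitations. Stable differences between children inflate the spread at T1, and adjusting for T0 removes them.

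The LSD step adds doubt about what is being compared. It can do something only if there are more than two groups, and the trial has two. Either the step is redundant, or the intended groups are arm-by-visit cells, for which one-way ANOVA is the wrong model.

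Two things are at stake: precision in a trial of 34 children, and the usefulness of its output for the next trial. An analysis without T0 does not give the baseline-adjusted residual SD needed to size that trial efficiently.

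**Working it through.** **The plan's own figure.** No power is stated. The one figure that can be reproduced is the recruitment target: 12 completers / (1 − 0.20) = 15 per arm, as stated.

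**Inputs.** From the documents: 18 v 16 randomised; 12 v 12 expected completers; P < 0.05 (the F test is two-sided). Assumed, because the documents give neither: a true effect d = 0.8 SD, and a T0-T1 correlation ρ from 0.2 to 0.7. Outcomes are taken as normal with equal SD at both visits.

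**Formula.** Power comes from the noncentral t distribution with noncentrality d / (s × √(1/n₁ + 1/n₂)), where s is the residual SD in units of the outcome SD:
- T1-only ANOVA: s = 1, df = N − 2
- ANCOVA on T0: s = √(1 − ρ²), df = N − 3
- ANOVA on change: s = √(2(1 − ρ)), df = N − 2

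**Example, 18 v 16.** √(1/18 + 1/16) = 0.344. T1-only noncentrality is 0.8 / 0.344 = 2.33, against a critical t of 2.037 on 32 df; power is 62%. ANCOVA at ρ = 0.7 has s = √0.51 = 0.714 and noncentrality 2.33 / 0.714 = 3.26, against 2.040 on 31 df; power is 89%.

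| d = 0.8 | 18 v 16 | 12 v 12 |
|---|---|---|
| T1-only ANOVA, any ρ | 62% | 47% |
| ANCOVA, ρ = 0.2 | 63% | 48% |
| ANCOVA, ρ = 0.3 | 66% | 50% |
| ANCOVA, ρ = 0.5 | 74% | 58% |
| ANCOVA, ρ = 0.7 | 89% | 74% |

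The formula ignores chance imbalance at T0. Simulation (20,000 runs per setting, 18 v 16) gives ANCOVA 65%, 73% and 87% at ρ = 0.3, 0.5 and 0.7, about 1 point lower each time.

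**Reading 1: two groups, T1 value.** LSD on two groups is the same test as the F test. T0 is unused, and the table shows the cost.

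**Reading 2: four arm-by-visit cells.** One-way ANOVA treats a child's two values as independent. The LSD comparisons are pairs of cells, and none is the between-arm difference in change. In simulation (18 v 16, d = 0.8), the omnibus F followed by LSD between arms at T1 has 53% to 55% power at ρ from 0.3 to 0.9, below the two-group T1 test. With no effect, the within-arm T1 v T0 comparison rejects in about 0.2% of runs at ρ = 0.5 and about 0% at 0.7. This should not be set against 5% alone: the omnibus gate by itself brings it to about 2% with independent cells. The rest of the drop comes from the ignored pairing.

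**Reading 3: change scores.** The change-score residual variance minus that of ANCOVA is 2(1 − ρ) − (1 − ρ²) = (1 − ρ)², which is never negative. So change scores are never more efficient than ANCOVA, apart from one degree of freedom. They are weaker than T1 alone when 2(1 − ρ) > 1, that is, when ρ < 0.5. At 18 v 16 and d = 0.8, power is 48%, 62% and 83% at ρ = 0.3, 0.5 and 0.7.

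**The case against.** The strongest reply is that nothing here is invalid. After randomisation, a two-group comparison at T1 is unbiased, and in simulation it rejects about 5% of the time under no effect. The trial is a pilot that claims no power, so the loss is measured against a better method and not against a target that the plan misses. This stands, and it limits the seriousness of the point.

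A reader might infer that the plan must either ignore T0 or treat the two visits as independent. The text does not support that: a one-way ANOVA on change is not excluded, and it would use T0 and respect the pairing. The wording about measured parameters does not suggest it, though, and LSD would still be redundant.

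A reader might also take the LSD step as proof that four cells are intended. Its stated trigger is a difference between the experimental and placebo groups, which are two groups. A redundant stock phrase explains it equally well, so the faults of the four-cell reading are conditional on that reading.

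Finally, a reader might conclude that much of the power is lost. That depends on a correlation the documents do not give. At 0.2 or below the gain from ANCOVA is under 2 points, and at 0.3 it is about 4.

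The point is not one merely left to an unseen analysis plan: the article names its test.

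**Conclusion.** The concern holds as a should-fix matter of efficiency and clarity. The only test named for the supplement's effect has no T0 covariate, its response variable is undefined, and it carries a post-hoc step that is redundant with two arms. On none of the three readings is it the efficient analysis.

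At d = 0.8 with 18 v 16, the gain from ANCOVA over T1-only ANOVA is about 4 points at correlation 0.3, 12 at 0.5 and 27 at 0.7. At 12 v 12 the corresponding gains are about 3, 11 and 28 points. Effect size, normality, equal SDs and correlation are all assumed. A sizeable correlation is plausible for age-dependent parameters given the age span, but it will differ between outcomes. The consequence reaches past this pilot because its results are to size the full trial.

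**What to change.** Replace the ANOVA and LSD sentences in the Statistical analysis section with:

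*Each laboratory and faecal outcome measured at T0 and T1 will be analysed by ANCOVA of the T1 value on randomised group, adjusting for the T0 value and for the stratification factors sex and age; the adjusted between-group difference with 95% CI will be reported.*

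Delete the LSD step. Serum tTG and faecal GIP are described under Diet control as checks of adherence to the gluten-free diet; if they go through the same model, label them as such.

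The change is to wording only and needs no new data. The T0 term costs one degree of freedom, and sex and age (as a linear term) cost two more. Going from N − 3 to N − 5 degrees of freedom lowers the ANCOVA powers above by less than 1 point, even if sex and age explain nothing beyond T0. The adjusted residual SD can then be carried into the sample size calculation for the full trial.

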### Research objective and hypothesis

We hypothesized that adherence to a GFD supplemented with oligofructose-enriched inulin would deliver health benefits to children suffering from CD without any side effects, and that it would alleviate intestinal inflammation, restore and stabilize balance of a gut microbiota and reverse nutritional deficiencies through enhanced absorption of vitamins and minerals. The main aim of this clinical trial is to evaluate the impact of an oligofructose-enriched inulin (Synergy 1) on selected biochemical parameters and nutritional status of paediatric CD patients following a GFD. Attempts are also being made to determine the influence of the oligofructose-enriched inulin supplement on the quantitative composition and the activity of intestinal microbiota.

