### Randomization and blinding

Patients have been randomly assigned to an intervention group (*n* = 18) or a placebo group (*n* = 16). Stratified randomization based on gender and age was conducted by a researcher not directly involved in the study. Separate randomization procedures were carried out for boys and for girls to produce comparable groups. The trial had a design where the researchers, laboratory personnel (excluding the researcher who distributed the supplement or the placebo to the participants) and the participants were not aware which subjects were receiving the supplement and which were receiving the placebo.

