### Dietary intervention

The patients of the intervention group received oligofructose-enriched inulin (Orafti® Synergy 1, Beneo, Tienen, Belgium) for 3 months, whereas children of the placebo group received maltodextrin (Maltodextrin DE 20, Hotrimex, Konin, Poland) during the same period. Synergy 1 (DP3–9: 50% ±10, DP ≥ 10: 50% ±10, according to the producer) is the commercially available preparation of chicory inulin enriched by a specific fraction of oligofructose produced by partial enzymatic hydrolysis of chicory inulin. Both supplements, Synergy 1 and maltodextrin, were similarly light yellow powders of slightly sweet taste. Both substances are approved food grade ingredients, and they have been previously used in other clinical trials [18, 19]. Synergy 1 and maltodextrin were packed in identical white disposable sachets by the outsourcing company (DorTech, Pobiedziska, Poland). During the enrolment visit (T0), each participant was provided with a package of sachets containing the appropriate supplement in the amount required for a 3-month intervention. The participants from the experimental group received sachets containing 10 g of oligofructose-enriched inulin, whereas the participants from the placebo group received packages containing 7 g of maltodextrin. The packages with the appropriate supplement were distributed by a researcher who was familiar with the identity of the groups. The participants were instructed to consume the contents of one sachet daily for 3 months while closely following a GFD. The medium for suspending the supplement (water, juice or yoghurt) was chosen by the participants and could be changed during the trial. The participants were also provided with a questionnaire of compliance and adverse reaction, and were asked to record their daily intake of the supplement, any adverse reactions (gastrointestinal and other) and any other drugs taken during the trial. The participants who did not consume the supplement for more than 80% of the trial period were eliminated from the study. Before the end of the intervention, all participants were asked to complete a brief questionnaire assessing their mental wellbeing and stool characteristic (frequency and consistency). In the questionnaire, they were asked to provide information based on the observations made in the last week of the supplement intake. The participants were also asked to complete a Food Frequency Questionnaire with 6 answers (FFQ-6). At the end of the 12-week intervention, the participants were asked to return any remaining sachets of the Synergy 1 supplement or the placebo for assessment of the compliance.

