### Sample size

To our knowledge, this study makes the first attempt to evaluate the effects of fructan supplementation on children with CD, therefore, it was performed as a pilot trial without calculating sample size. Our plan was to recruit approximately 30 children (15 subjects per arm) with diagnosed CD on the assumption that the drop-out rate would reach approximately 20% (12 participants in each arm would complete the trial). The results obtained in the pilot study will be used to calculate the sample size for a fully-powered study that will be carried out in the future on paediatric CD patients receiving oligofructose-enriched inulin with GFD.

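### The above-80% intake rule carries no exception for side effects, so the planned percentages can omit children who stopped because of intolerance

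*Protocol article*

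**What the plan says.** Three parts of the protocol article bear on this.

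- **Research objective and hypothesis.** The supplemented diet "would deliver health benefits to children suffering from CD without any side effects". Tolerability is therefore part of what was hypothesised, although the main aim concerns biochemical parameters and nutritional status.
- **Dietary intervention.** Every participant was asked to "record their daily intake of the supplement, any adverse reactions (gastrointestinal and other) and any other drugs taken during the trial". The same section then says: "The participants who did not consume the supplement for more than 80% of the trial period were eliminated from the study".
- **Statistical analysis.** The analysis population is fixed by one sentence: "The participants whose reported intake of the Synergy 1 supplement or the placebo exceeded 80% of the prescribed intake will be included in final analyses". Later in that section comes the only sentence on side effects: "The side effects of supplementation will be expressed by the percentage of each effect noted in the experimental group or the placebo group". It names no separate population.

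On numbers, the section on randomization and blinding gives 18 children in the intervention group and 16 in the placebo group. The section on sample size planned for 15 per arm and assumed that "the drop-out rate would reach approximately 20% (12 participants in each arm would complete the trial").

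**The concern.** Intake is observed after randomisation and can itself be a consequence of a side effect. A child who gets abdominal symptoms from a daily powder may well stop taking it or skip sachets. A filter on intake can then remove the very events that a side-effect table exists to count. If intolerance were commoner on the active supplement, the intervention percentage would lose more events than the placebo percentage, and the comparison between arms would be distorted as well.

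At stake is how a favourable table would be read. A low or zero percentage among children who managed to take more than 80% of their sachets describes tolerability in those who tolerated the product. It is weak support for a hypothesis about all children given it, and the article expects its findings to inform supplementation guidelines for children.

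**Working it through.** **1. The plan's own figure.** 15 per arm with 20% drop-out: 15 × (1 − 0.20) = 12 completers per arm. This reproduces the stated 12. There is no power calculation to check.

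**2. Who is lost under the rule.** Twelve weeks is 84 days at one sachet a day, and 0.80 × 84 = 67.2. To exceed 80%, a child must take at least 68 sachets (68/84 = 81.0%; 67/84 = 79.8%). A child with full intake until about day 67 or earlier who then stops is excluded, as is one who skips that many sachets in total. A child who stops later stays in.

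**3. How many that could be.** The assumed 20% drop-out applied to the 18 intervention children is 0.20 × 18 = 3.6, that is 3 to 4. The article does not say why children would drop out, so the number who stop with a side effect is an assumption. I use 0 to 4.

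**4. Case in which no retained child has the effect.** With *d* children excluded, all having had the effect, the plan reports 0/(18 − *d*). The figure on all randomised children is *d*/18.

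| Excluded with the effect (*d*) | Reported under the rule | All 18 randomised | Exact 95% CI on all 18 |
|---|---|---|---|
| 0 | 0/18 = 0% | 0/18 = 0% | 0 to 18.5% |
| 1 | 0/17 = 0% | 1/18 = 5.6% | 0.1 to 27.3% |
| 2 | 0/16 = 0% | 2/18 = 11.1% | 1.4 to 34.7% |
| 3 | 0/15 = 0% | 3/18 = 16.7% | 3.6 to 41.4% |
| 4 | 0/14 = 0% | 4/18 = 22.2% | 6.4 to 47.6% |

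**5. Cases in which some retained children also have the effect.** Four excluded, all with the effect:

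- 3 of the 14 retained affected: 3/14 = 21.4% reported, against (3 + 4)/18 = 38.9%.
- 4 of the 14 retained affected: 4/14 = 28.6% reported, against (4 + 4)/18 = 44.4%.

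**6. The direction is not guaranteed.** Suppose four are excluded for reasons unrelated to side effects, none had the effect, and 2 of the 14 retained did. The plan then reports 2/14 = 14.3%, against 2/18 = 11.1% on everyone. The rule understates the rate when the effect is commoner among the excluded than among the retained, and overstates it in the reverse case.

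**7. What zero events would show.** The exact two-sided 95% upper limit for 0/*n* is 1 − 0.025^(1/*n*):

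- *n* = 18: 18.5%
- *n* = 14: 23.2%
- *n* = 12: 26.5%

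The one-sided 95% limit, 1 − 0.05^(1/*n*), is 15.3% for *n* = 18 and 22.1% for *n* = 12.

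**The case against.** The best defence is that the side-effect sentence does not state its denominator. It speaks of effects noted in the two groups, which were defined at randomisation as 18 and 16, and the intake restriction may have been meant only for the measured laboratory parameters. The elimination sentence is also loosely worded and could be taken to remove only children who missed more than 80% of the period. This stands as far as it goes: restriction of the side-effect table to compliers is inferred, not written. But the sentence on final analyses is unqualified, sits in the same section, and sets the limit clearly at above 80%. If all randomised children were meant, the text needs to say so.

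Four further readings are tempting and are not supported.

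- *Every child who stops for a side effect disappears.* Only those ending at 80% intake or less do.
- *The no-side-effects hypothesis cannot be tested at all.* One event in a retained child would still contradict it. What is lost is the ability to support it validly.
- *The active-arm rate will be understated.* The article gives no reasons for drop-out, and step 6 shows that the shift can go the other way.
- *The article plans to claim safety.* The wording is a hypothesis, and the stated conclusions make no safety claim.

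Nor is it an error that the article gives no intervals or between-arm contrast for side effects. Percentages by arm are a normal summary for a pilot without a sample size calculation, and such detail is commonly left to a fuller document. The participant flow figure is not available here, so I do not conclude that reasons for discontinuation go unreported.

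**Conclusion.** The point holds for the analysis population. Followed as written, the two intake sentences take children at or below 80% out of the side-effect percentages, with nothing to keep in those who reached that level because of intolerance. This can understate side effects and makes a low percentage poor evidence for the hypothesis.

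The size cannot be derived from the article. With drop-out at the assumed 20%, 0 to 4 intervention children excluded with the effect and none affected among those retained, a reported 0% corresponds to between 0% and 22% of all 18. This rests on three assumptions: the planning drop-out applies to the 18 actually randomised, it coincides with falling to 80% intake or less, and the side-effect percentages use the same population as the other final analyses. The upper end treats the whole expected drop-out as symptomatic and is an extreme case. Separately, zero events among all 18 would still be compatible with a true rate of up to 18.5%.

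**What to change.** Add one sentence to the statistical analysis section: side effects are summarised for every randomised child who took at least one sachet, by assigned group and regardless of compliance, as n/N for each effect, preferably with exact 95% confidence intervals. Add a listing, by arm and with reasons, of children who stopped or were eliminated. Keep the above-80% set as a secondary presentation of side effects. State that if an effect is not observed, the result will be given as the upper confidence limit (18.5% two-sided for 0/18) rather than as absence of side effects. The hypothesis itself need not be rewritten.

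The cost is small. All participants were given the diary, so no new instrument is needed. However, the article describes only the return of leftover sachets at the end of the intervention. It does not say that the diaries of eliminated children were kept or recovered, so these may have to be retrieved, and any that are missing should be counted and reported. The resulting rates may be less favourable than those among compliers.
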